### 5.3. Visit 2a (Day 3± 1) – CPK Monitoring

Creatine kinase (CPK) monitoring will be performed in 10 subjects in Part I for 1st vaccination on Day 3 with an allowed a time window of 1 day. Whole blood sample for CPK test will be collected and analyzed by local laboratory.

### 5.4. Visit 3 (Day 14+3) – Safety screening

A safety screening will be conducted for second vaccination on Day 14 with an allowed delay of 3 days. The following study procedures should be performed in this visit.

- (1) Check withdrawal criteria.
- (2) Check contraindications to second vaccination.
- (3) Conduct a complete physical examination with an exception of body height. Measure and record the oral temperature.
- (4) Collect approximately 8 ml of whole blood sample for following local laboratory tests.
  - Hematological tests: the same as screening visit
  - Biochemistry tests: the same as screening visit

\* Re-test may be conducted 1 week later (see [Section 4.3.2](#)).
- (5) Record concomitant medication(s)/vaccine(s) taken since the previous visit.
- (6) Record and report adverse or serious adverse event if any one has occurred since the previous visit.

### 5.5. Visit 4 (Day 21+3) – 2nd vaccination

The second dose of study vaccine should be administrated on Day 21 with an allowed delay of 3 days. All subjects should complete the following study procedures **prior to vaccination**.

- (1) Check withdrawal criteria.
- (2) Check contraindications to second vaccination.
- (3) Conduct a complete physical examination with an exception of body height. Measure and record the oral temperature.
- (4) Collect urine samples for pregnancy test (in females of childbearing potential only).
- (5) Collect approximately 7 ml of whole blood sample for following central laboratory tests.
  - Immunogenicity tests: IgG and neutralizing antibody titers.

The study vaccine will be administrated intramuscularly (i.m.) in the deltoid of the non-dominant arm. **After vaccination:**

- (1) Observe closely during vaccination and at least 2 hours after vaccine administration. An appropriate medical treatment should be readily available in case of a rare anaphylactic reaction following vaccination.
- (2) Conduct a telephone follow-up 7 days after vaccine administration. For subjects in Block C, a 14-day telephone follow-up will also be taken place.
- (3) Collect the diary card of 1st vaccination. The investigator or delegate will verify completion. The information will be transcribed into the CRF. Any unreturned diary cards will be sought from the subjects through telephone call(s) or any other convenient procedure.
- (4) Dispense self-evaluation diary card for 2nd vaccination. Instruct the subjects to monitor body temperature and complete the diary correctly. Any solicited symptoms and local and/or general adverse events occurring during a 7 days post-vaccination period, and any unsolicited symptoms occurring during a 21 days post-vaccination period will be recorded on the diary card. The subjects will be instructed to contact the investigator or their delegates immediately if symptoms should manifest or in case of any signs or symptoms occurring which the subject perceives as serious. Record concomitant medication(s)/vaccine(s), taken since the previous visit and during vaccination period.
- (5) Record and report adverse or serious adverse event if any one has occurred since the previous visit.

## **5.6. Visit 4a (Day 24± 3) – CPK Monitoring**

Creatine kinase (CPK) monitoring will be performed in 10 subjects in Part I for 2nd vaccination on Day 24 with an allowed a time window of 3 day. Whole blood sample for CPK test will be collected and analyzed by local laboratory.

Whether Visit 2a and Visit 4a should be conducted again in Part II based on the Part I results and judged by DSMB.

## **5.7. Visit 5~7 – Follow-up**

There will be three follow-up visits for each participant. The first one will be conducted in the hospital and the other two will be conducted through telephone contact.

### **5.7.1. Visit 5 (Day 42±3)**

Visit 5 will be conducted on Day 42 with a time window of 3 days. The following study procedures will be completed during this period.

- (1) Check withdrawal criteria.
- (2) Conduct a complete physical examination with an exception of body height. Measure and record the oral temperature.
- (3) Collect approximately 8 ml of whole blood sample for following local laboratory tests.
  - Hematological tests: the same as screening visit
  - Biochemistry tests: the same as screening visit
- (4) Collect approximately 7 ml of whole blood sample for following central laboratory

tests.

- Immunogenicity tests: IgG and neutralizing antibody titers, and epitope mapping.
- (5) Collect the diary card of 2nd vaccination.  
The investigator or delegate will verify completion. The information will be transcribed into the CRF. Any unreturned diary cards will be sought from the subjects through telephone call(s) or any other convenient procedure.
  - (6) Record concomitant medication(s)/vaccine(s), taken since the previous visit.
  - (7) Record and report adverse or serious adverse event if any one has occurred since the previous visit.

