#### **4.3.2. Contraindications to second vaccination**

The following conditions constitute a contraindication to vaccination and those should be

checked prior to second vaccination (at Visit 3 and Visit 4):

(1) Subject with any abnormal laboratory results\* at safety screening visit (Visit 3):

\* Subject with ALT/AST or creatinine  $> 1 \times \text{ULN}$  but  $< 2.5 \times \text{ULN}$  could be re-tested 1 week later.

(2) Pregnancy

(3) Subject with fever defined as oral temperature  $\geq 37.5^{\circ}\text{C}$  at the time before second vaccination.

(4) Subject with acute disease at the time before the second vaccination (defined as the presence of a moderate or severe illness\*\* with or without fever).

\*\* All vaccines can be administered to persons with a minor illness such as diarrhea, mild upper respiratory infection with low-grade febrile illness, i.e. oral temperature  $< 37.5^{\circ}\text{C}$ .

Once a subject meets any of the contraindication, the second vaccination can be administrated at the later day, within a 3-day delay (Day 21 to Day 24), or be withdrawn at investigator's discretion. The investigator should document on the Vaccination page of the CRF, the possible reasons for delay administration/withdrawal (AE, SAE or other) and whether the decision to discontinue further vaccination was made by the subject or the investigator.

Any subject who receive the vaccination with dosage deviation or who does not receive the second vaccination on schedule may not necessarily be withdrawn from the study as further study procedures and the follow-up visits may be performed.

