| Distribution                            |                | X                              |                   |                     | X                              |                   |                  |                      |                                 |
| Return                                  |                |                                |                   |                     | X                              |                   | X                |                      |                                 |
| Concomitant medications                 | X              | X                              |                   | X                   | X                              |                   | X                | X *       | X *                  |
| Adverse events                          |                | X                              |                   | X                   | X                              |                   | X                | X *       | X *                  |
| Study completion                        |                |                                |                   |                     |                                |                   |                  |                      | X *                  |

 Body height will be only measured at Visit 1.

 Pregnancy test will be only conducted in female subject of childbearing potential.

 Hematology tests include CBC, such as Hb, Hct, RBC count, WBC count, WBC differential and platelet count.

 Biochemistry tests include ALT, AST, γGT, alkaline phosphatase, total bilirubin, total protein, albumin, BUN, creatinine, uric acid, total cholesterol, triglyceride and glucose (fasting).

† These procedures should be conducted before vaccination.

\* These study procedures will be conducted through telephone contact. \*\* For subjects in Block C, a 14-day telephone follow-up will also be taken place. ^ Creatine kinase (CPK) assay at Visit 2a and Visit 4a in Part I should be monitored at the 3rd days after each vaccination, the results should be evaluated by DSMB to decide if CPK should be monitored in Part II.

# ET: early termination (The final telephone follow-up may be omitted if a subject is withdrawn as a reason other than safety.)

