**Table 5-2 Intervals between study visits:**

| Interval               | Length of interval |
|------------------------|--------------------|
| 1 (Visit 1 → Visit 2)  | Within 7 days      |
| 2 (Visit 2 → Visit 2a) | 3 ± 1 days         |
| 3 (Visit 2 → Visit 3)  | 14 + 3 days        |
| 4 (Visit 2 → Visit 4)  | 21 + 3 days        |
| 5 (Visit 2 → Visit 4a) | 24 + 3 days        |
| 6 (Visit 2 → Visit 5)  | 42 ± 3 days        |
| 7 (Visit 2 → Visit 6)  | 126 ± 14 days      |
| 8 (Visit 2 → Visit 7)  | 210 ± 14 days      |

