#### 7.3.4.2 Unsolicited symptoms

An unsolicited local and general AE or symptoms are the one whose nature or intensity is NOT consistent with the expected AEs described and listed above in this protocol. Information of unsolicited symptoms/AEs will be collected during a 21-day follow-up period after each vaccination (i.e. day of vaccination and 20 subsequent days) and reported at each visit.

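### Visit 5 is counted from Day 0 although dose 2 may fall on Day 21 to 24, so the second diary can be collected 1 to 5 days before its 21-day window closes; the Visit 4a windows also disagree

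*Protocol*

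**What the plan says.** **Dose 2.** Protocol Section 5.5: "The second dose of study vaccine should be administrated on Day 21 with an allowed delay of 3 days". Section 4.3.2 gives the same limits for a dose postponed because of a contraindication: "within a 3-day delay (Day 21 to Day 24".

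**Visit 5.** Section 5.7.1: "Visit 5 will be conducted on Day 42 with a time window of 3 days". Table 5-2 lists the interval as "Visit 2 → Visit 5", so it runs from the first dose. Table 5-1 prints the range as Day 39 to 45. The diary card for the second dose is collected at this visit, and it is the only visit with an immunogenicity sample after dose 2 (Section 3.2).

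**Unsolicited events.** Section 7.3.4.2 has them "collected during a 21-day follow-up period after each vaccination (i.e. day of vaccination and 20 subsequent days". Section 5.5 places them on the diary card, and Section 9.1 makes them part of the primary endpoint.

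**Visit 4a (CPK).** The protocol describes the timing in three ways:
- Section 5.6: second "vaccination on Day 24 with an allowed a time window of 3 day", headed as Day 24±3.
- The synopsis flow chart, Table 5-1 and Table 5-2: 24+3, that is Day 24 to 27, with Table 5-2 counting it as "Visit 2 → Visit 4a".
- The footnotes to the flow chart and Table 5-1: CPK "should be monitored at the 3rd days after each vaccination". Synopsis Section VIII also names the third day.

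**The concern.** Two clocks are in use. The diary window runs from the actual second dose, while the visit that closes the diary runs from the first dose. Any delay of dose 2 shortens the time between them. Delay is not exotic here: Section 4.3.2 allows a re-test one week after Visit 3 (Day 14 to 17), which lands on Day 21 to 24.

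The first dose has no such problem. Its window closes on Day 20 and its card is returned at Visit 4, Day 21 to 24. Diary follow-up can therefore be complete after dose 1 and incomplete after dose 2, and can differ between subjects who all comply with the protocol. At stake is the quality of a primary safety endpoint. Section 10.5 makes no provision for missing data.

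The titre at Visit 5 is analysed as a single Day 42 value against baseline (Section 10.4.1), yet it mixes different times since dose 2.

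The CPK results from 10 Part I subjects inform the DSMB's decision on CPK monitoring in Part II. A draw before dose 2 says nothing about dose 2, and Section 5.6 as worded permits one.

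**Working it through.** **Inputs**
- Dose 2 day d = 21, 22, 23 or 24 (Sections 5.5 and 4.3.2).
- Visit 5 day v = 39 to 45 (42±3; Section 5.7.1, Tables 5-1 and 5-2).
- Last day of the dose 2 diary window = d + 20 (Section 7.3.4.2).
- Visit 4a day w = 24 to 27 (tables) or 21 to 27 (Section 5.6).

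**Reproducing the plan's own ranges.** 21+3 gives Day 21 to 24, 24+3 gives Day 24 to 27 and 42±3 gives Day 39 to 45. All three match the ranges printed in Table 5-1.

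**Visit 5 against the diary window.** The time since dose 2 is v − d. The shortfall is (d + 20) − v where that is positive.

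| Dose 2 day | Window closes | Days from dose 2 to Visit 5 | Visit 5 days that are too early | Shortfall in days | Shortfall at Day 42 |
|---|---|---|---|---|---|
| 21 | 41 | 18–24 | 39, 40 | 2, 1 | 0 |
| 22 | 42 | 17–23 | 39–41 | 3, 2, 1 | 0 |
| 23 | 43 | 16–22 | 39–42 | 4, 3, 2, 1 | 1 |
| 24 | 44 | 15–21 | 39–43 | 5, 4, 3, 2, 1 | 2 |

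Overall the time since dose 2 runs from 39 − 24 = 15 to 45 − 21 = 24 days. Early pairs: 2 + 3 + 4 + 5 = 14 of 4 × 7 = 28. This counts a Visit 5 on the last window day as complete.

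**Two causes.** With dose 2 on Day 21 there is no delay, yet Visit 5 on Day 39 or 40 is already 2 or 1 days short. That part comes from the −3 tolerance. The rest comes from the Day 0 anchor. Re-anchoring at dose 2 + 21±3 gives 18 to 24 days, and 20 − 18 = 2 days could still be missed.

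**What remains after Visit 5.** The next contact is Visit 6 by telephone, Day 112 to 140. That is at least 112 − 45 = 67 days after Visit 5.

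**Visit 4a.** The time since dose 2 is w − d.
- Tables (24 to 27): from 24 − 24 = 0 to 27 − 21 = +6 days. Of 4 × 4 = 16 pairs, none precedes dose 2, 1 is on the same day and 4 are on the third day.
- Section 5.6 (21 to 27): from 21 − 24 = −3 to 27 − 21 = +6 days. Of 4 × 7 = 28 pairs, 6 precede dose 2 and 4 are on the same day.
- Third day after dose 2: d + 3 = 24, 25, 26 or 27, which lies inside both windows.

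**The case against.** **Adverse events are not lost.** A reader might infer that up to 5 of the 21 days of follow-up vanish. The documents do not support that. Section 5.7.2 has Visits 6 and 7 record any event since the preceding visit, Section 7.3.5 has events sought at each telephone contact, and Section 7.3.5.2 follows them to Day 210. Subjects are also told to report symptoms at once (Section 5.5). An event in the missed days can be recorded with its onset date and counted. This stands. What is left is weaker recording: a nightly diary gives way to non-directive questioning at least 67 days after Visit 5.

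**The CPK statements can be met together.** A reader might infer that the three descriptions are mutually impossible. They are not: a draw on dose 2 + 3 days satisfies all of them for every permitted dose day. A draw before dose 2 is possible only under Section 5.6. Nor does the protocol say how fast CPK responds, so nothing can be claimed on that score. The disagreement between ±3 and +3 remains, as does the fact that either window permits draws off the stated third day.

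**The titre effect is modest.** With dose 2 on Day 21 the range is already 18 to 24 days; the anchor extends it down to 15. Both groups share the same schedule, titres are secondary and compared within subject, and Appendix I requires vaccination and sampling times to be logged. No bias between dose groups is shown. This stands too.

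**The pair count is not a risk.** A reader might take 14 of 28 as half the subjects. It counts permitted calendar combinations; the larger shortfalls need a late dose and an early visit together.

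**Conclusion.** The point holds in limited form. A fully compliant site can collect the second diary 1 to 5 days before the unsolicited-event window closes. With dose 2 on Day 23 or 24, even a visit on the nominal Day 42 is 1 or 2 days early. The harm is reduced prospective recording and poorer recall for part of a primary endpoint, not absent follow-up. The single post-dose-2 titre has an avoidable spread of 15 to 24 days since dose 2.

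Separately, Section 5.6 contradicts the flow chart and Tables 5-1 and 5-2 on the Visit 4a window, and neither window by itself enforces the third-day requirement.

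This rests on the windows as printed and on the diary being handed in at Visit 5. How often subjects would fall in the affected combinations cannot be derived from the protocol. Because events are followed to Day 210 and no hypothesis is tested on the primary endpoint (Section 10.3.2), this is something that should be fixed rather than a flaw that undermines the trial.

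**What to change.** 1. In Table 5-1 (and the matching synopsis flow chart), Table 5-2 and Section 5.7.1, count Visit 5 from the actual date of dose 2.
2. Set its lower limit no earlier than the close of the 21-day diary window. Re-anchoring alone with ±3 kept is not enough. As Section 7.3.4 has the diary completed each evening, a lower limit of dose 2 + 21 days would secure the last entry; with the upper limit at dose 2 + 24 days, Visit 5 would fall on study Day 42 to 48.
3. Reconcile the Visit 4a window in Section 5.6 with the flow chart and Tables 5-1 and 5-2, and all of them with the stated third day after vaccination, counted from the actual date of dose 2.

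The cost is amendment wording in the tables and two sections. Some Visit 5 dates move a few days later. No visit or blood draw is added.

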### 5.7.2. Visit 6 and 7 (Day 126±14 and 210±14) – Telephone follow-up

Visit 6 and Visit 7 will be conducted on Day 126 and 210, respectively. A 14-day time window will be allowed. The following study procedures should be completed and all the information will be collected through telephone call(s).

- (1) Check withdrawal criteria (only at Visit 6).
- (2) Record concomitant medication(s)/vaccine(s), taken since the previous visit.
- (3) Record and report adverse or serious adverse event if any one has occurred since the previous visit.
- (4) Complete the Off Study CRF at the final visit.

## 5.8. Early termination (ET)

For subjects who discontinue this study earlier, a final telephone follow-up may be arranged as soon as possible and all study procedures listed for the final visit (Visit 7) should be completed. However, if a subject is withdrawn at regular return as a reason other than AE, the telephone follow-up could be omitted and no further information has to be collected since last visit.

## 6. Study Drug

### 6.1. Treatment assignment

After the informed consent document is signed, all subjects will be assigned the screening number in turn. Only qualified subjects will be uniquely identified by a combination of a 1-digit center number and a 3-digit subject number. The subject numbers will be given in a consecutive order, i.e. initiate from 001 and subsequently follow by 002, 003... etc. Each subject number will randomly correspond to one of the dosing groups below.

- **Group A05:** 0.25 ml per dose (5 µg total protein + adjuvant 150 µg AlPO4)
- **Group B10:** 0.5 ml per dose (10 µg total protein + adjuvant 300 µg AlPO4)

The corresponding study group of individual subject will be recorded in a sealed envelope. It could be opened only before the first vaccination. Both the subject numbers and corresponding dosage should be recorded on the CRF.

Once a number has been assigned, it could not be replaced by other subject.

This study contains two parts, and there are three and one blocks in Part I and Part II, respectively. The blocks will be initiated in turn as well and the randomization will be conducted for each block separately. For the first part, the first subject enrolled will be assigned to Block A, and the subsequent 2 and 7 subjects will be assigned to Block B and C. After that, the rest 50 subjects will be assigned to Block D for the second part of study (Table 6-1).

Randomization scheme will be created by Qualitix Biostatistics & Data Management (BDM). The first eligible subject, 1-001, will be assigned to low-dose group (Group A05) for the consideration of safety. After that, the allocation of study dosage will be conducted through randomization scheme in order to insure that assignment is unbiased and concealed from subjects and investigator staff.

**Table 6-1** Number of participants assigned to each block:

| Part (Total number)                                                       | Block (Total number)                              | Administration assigned |                    |
|---------------------------------------------------------------------------|---------------------------------------------------|-------------------------|--------------------|
|                                                                           |                                                   | Group                   | Number of Subjects |
| Part I
(n = 10, in 1 center)                                           | A (n = 1, 1-001)                                  | A05                     | 1                  |
|                                                                           | B (n = 2, 1-002 and 1-003)*                       | A05                     | 1                  |
|                                                                           |                                                   | B10                     | 1                  |
|                                                                           | C (n = 7, 1-004 to 1-010)**                       | A05                     | 3                  |
|                                                                           |                                                   | B10                     | 4                  |
| Part II
(n = 50, in 2 centers)                                         | D (n = 50, 1-011, 1-012...
2-011, 2-012...)*** | A05                     | 25                 |
|                                                                           |                                                   | B10                     | 25                 |
| * Initiate 7 days safety monitoring after 1 st vaccination.    |                                                   |                         |                    |
| ** Initiate 7 days safety monitoring after 2 nd vaccination.   |                                                   |                         |                    |
| *** Initiate 14 days safety monitoring after 2 nd vaccination. |                                                   |                         |                    |

## 6.2. Treatment blinding

Not applicable. This is an open-label study.

## 6.3. Description of study vaccine

This is a Phase I, open-label study. After enrollment, all subjects will be randomized to 2 treatment groups, Group A05 or Group B10, in a 1:1 ratio. Both groups will follow the same visit structure and be administrated 2 doses of the study drug, EV71vac. The information of the study drugs is described as following.

### ◆ Development:

To carry-on the development of a vaccine against EV71 infection, Vaccine Research and Development Center (VRDC) at NHRI has the basic technology through technology transfer agreement with Taiwan CDC, NHRI VRDC has made significant research progress in the serum-free bioprocess for producing cell-cultured-based inactivated whole-virion EV71 candidate vaccine using the roller-bottle technology. The seed virus strain and Vero cells which had been cultivated at Taiwan CDC then

transferred to NHRI VRDC for further development. Vero grown, purified and formaldehyde-inactivated whole virus candidate vaccine was developed and produced in a GCP certified facility of VRDC, NHRI in Taiwan.

- ◆ Active ingredient: Inactivated EV71 whole virion (EV71vac bulk)
- ◆ Dosage form:

The EV71vac is harvested, ultra-concentrated, purified and inactivated with formalin, and is formularized with aluminum (AlPO4). It contains 20 µg/ml viral protein with adjuvant 600 µg/ml AlPO4.

The vaccine is formulated as a multi-dose injection, 3 ml sterile suspension per vial, and each vial will be applied for maximum 5 doses at the same time.
- ◆ Dose:
  - **Group A05:** 0.25 ml per dose (5 µg total protein + adjuvant 150 µg AlPO4)
  - **Group B10:** 0.5 ml per dose (10 µg total protein + adjuvant 300 µg AlPO4)
- ◆ Pharmacological category: Vaccine
- ◆ Mechanism of action: Preventive vaccination of inactivated EV71 whole virion (EV71vac bulk) to induce antibody against EV71 virus.
- ◆ Appearance: Opalescent liquid
- ◆ Storage: 2-8°C, do not freeze
- ◆ Manufacture: Vaccine Research and Development Center (VRDC) of National Health Research Institute (NHRI)

Study vaccine will be packaged in appropriate bags labeled with protocol number, name of study center, name of study medication, manufacture date, storage condition and dosing instruction. The warning of “For use in the specified clinical study only” and “Far away from the children” will be labeled.

It is noted that the investigators and/or pharmacists must maintain records of the product's delivery to the study site, the inventory at the site, and use by each subject, and the return to the sponsor or alternative disposition of unused product(s). These records will include dates, quantities, batch/serial numbers and the unique code numbers assigned to study subjects. Investigators will maintain records that document adequately that subjects were provided the doses specified by the protocol and reconcile all investigational products received from the sponsor. At the time of return to the sponsor, investigators must verify that all unused or partially used drug supplies have been returned by the clinical study subjects and no remaining supplies are in the investigators' possession.

